**Methods/Design:**

After approval by their institutional review board, three hospitals will enroll 120 patients undergoing major abdominal surgery in a randomized, double-blind, phase III study. After a 24-h CWI of ropivacaine 0.2 % + methylprednisolone 1 mg/kg, patients will be randomly assigned to receive either ropivacaine + steroid or placebo for the next 24 h. Then, patient-controlled CWI with only ropivacaine 0.2 % or placebo (according to the group of randomization) is planned after 48 h up to 7 days (bolus 10 ml, lock-out 1 h, maximum dose of 40 ml in 4 h). Morphine equivalent consumption up to 7 days will be analyzed, together with any catheter- or drug-related side effect. Persistent post-surgical pain (PPSP) incidence will also be investigated. Our primary endpoint is analgesic consumption in the first 7 days after surgery; we will evaluate, as secondary endpoints, any catheter- or drug-related side effect, genotype/phenotype correlations between some polymorphisms and postoperative outcome in terms of morphine consumption, development of the inflammatory response, and incidence of PPSP. Finally, we will collect, in a subgroup of patients, wound exudate samples by micro-dialysis, blood samples, and urine samples up to 72 h to investigate local and systemic inflammation and oxidative stress.

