### Procedures - genetic study

We will genotype several SNPs in *ADRB2*, *OPRM1*, *COMT*, *UGT2B7*, and *IL-1Ra* genes in all patients by the Taqman SNP Genotyping Assays (Applied Biosystems, Foster City, CA, USA) in the Pain-OMICS core-lab of Azienda Ospedaliera of Parma.

The peripheral blood samples are collected during general anesthesia into EDTA-coated tubes. We extract DNA by using a QIAamp DNA Blood Mini Kit (Qiagen, Hilden, Germany) from 200 μl of blood. DNA obtained are stored at −20 °C for subsequent TaqMan analysis. Amplification is performed in a volume of 5 μl containing 10 ng of genomic DNA, SsoFast Probes Supermix (Bio-Rad Laboratories S.r.l, Segrate, Italy). Cycling and hybridization conditions are set in accordance with the instructions of the manufacturer.

The amplification and genotyping discrimination are performed in a LightCycler 480 Real-Time PCR System (Roche Diagnostics Ltd, Lewes, UK). All assays are used in accordance with the instructions of the manufacturer (Life Technologies, Monza, Italy). The SNP calling is made with LightCycler 480 Endpoint Genotyping software version 1.5.0.39 (Roche Diagnostics Ltd).

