### Statistics

Sample size calculation was made on the hypothesis that the average morphine equivalent consumption in patients receiving local anesthetic and steroids CWI will be reduced by 50 % as compared with those in the control group. This assumption comes from (1) our retrospective experience and audits about analgesic consumption in our institution and (2) data from previous literature [27]; they both showed reduction in morphine consumption of 30–50 % in patients receiving local anesthetic wound infusion. Given this assumption, we need 50 patients per group for a power of 80 % and an α error of 5 %; given an attrition rate of 15–20 %, 120 patients are needed in each group.

We will perform an intention-to-treat analysis, and all participants will be analyzed once enrolled. We consider a “dropout” to be any patient not completing the evaluation at 3 months (for any reason).

For descriptive variables, we plan to use mean and standard deviation for normally distributed variables and average interquartile range for skewed distributions.

We will perform group comparison by using the Student’s *t* test or Mann–Whitney test for quantitative variables and Pearson’s chi-squared test for categorical variables. Inflammation, oxidative stress, and genetic background will be assessed to see whether they are biological markers that help modulate post-operative and persistent pain: the difference in inflammatory response and oxidative stress will be analyzed by means in a uni- and multi-variate regression model for repeated measures, including time, group, and their interaction. Variables will be transformed if needed to satisfy model assumptions. Post-hoc comparisons will include within-group changes over time and between-group differences at each assessment. The *P* value will be adjusted for multiple tests. Fisher exact test will be used to evaluate the impact of genetic background. The odds ratio and 95 % confidence interval will be computed with logistic regression. The *P* value to assess statistical significance will be corrected with the Bonferroni correction depending on the number of candidate genes tested.

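### The Bonferroni divisor for the genetic tests counts genes, but the tests are of SNPs against several phenotypes, so the stated correction does not hold the error rate at 5 %

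*Protocol article*

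**What the plan says.** Four places in the protocol article bear on this.

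- **Procedures - genetic study:** "We will genotype several SNPs in *ADRB2*, *OPRM1*, *COMT*, *UGT2B7*, and *IL-1Ra* genes in all patients". That is five genes. The number of SNPs, in total or per gene, is not given.
- **Abstract, Methods/Design:** genotype is to be related to "postoperative outcome in terms of morphine consumption, development of the inflammatory response, and incidence of PPSP". That is three phenotypes, two quantitative and one binary. Study outcomes adds an analysis of polymorphisms in combination.
- **Statistics, method:** "Fisher exact test will be used to evaluate the impact of genetic background", followed by "The odds ratio and 95 % confidence interval will be computed with logistic regression". Earlier in the same paragraph, the t test or Mann-Whitney test is given as the general rule for quantitative variables.
- **Statistics, multiplicity:** the genetic P value is to be "corrected with the Bonferroni correction depending on the number of candidate genes tested". A separate sentence promises adjustment for multiple tests without naming a method. It follows the post-hoc comparisons of the repeated-measures model and concerns those, not the genetic tests.

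**The concern.** Bonferroni holds the family-wise error when the divisor is the number of tests in the family. Here the divisor is the number of genes, while the unit tested is a SNP against a phenotype. The two counts agree only with one SNP per gene and one phenotype. The article plans several SNPs and names three phenotypes.

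Genotype/phenotype correlation is a listed secondary endpoint, and the Discussion asks whether polymorphisms might serve as biomarkers of postoperative pain and opioid use. The authors chose to control the error of these tests. A reader who sees the word Bonferroni will take a result at P < 0.01 as protected at 5 %, and the rule as written does not give that protection.

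**Working it through.** **Inputs.** The overall level is 5 %. The article states this only for the sample size ("we need 50 patients per group for a power of 80 % and an α error of 5" %), so its use for the genetic tests is an assumption. Genes: 5 (genetic procedures). Phenotypes: 3 (abstract). SNPs per gene: not given; 1 to 3 is assumed.

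The article gives no numeric threshold or error rate for these tests, so there is no stated figure to reproduce.

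**Step 1: threshold as written.** 0.05/5 = 0.01.

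**Step 2: family-wise error.** For m independent tests of exact size 0.01, it is 1 − 0.99^m, with m = 5 × SNPs per gene × phenotypes in the family.

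| SNPs per gene | One phenotype: m | Error | Three phenotypes: m | Error |
|---|---|---|---|---|
| 1 | 5 | 4.9 % | 15 | 14.0 % |
| 2 | 10 | 9.6 % | 30 | 26.0 % |
| 3 | 15 | 14.0 % | 45 | 36.4 % |

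Only the first cell holds 5 %.

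**Step 3: correlation.** A multivariate-normal simulation of the three-phenotype case, with an assumed correlation of 0.8 between SNPs of one gene and 0.5 between phenotypes, gives about 13 %, 20 % and 26 % for 1, 2 and 3 SNPs per gene.

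**Step 4: conservatism of Fisher's test.** I enumerated 2×2 tables exactly, adding up the binomial probabilities of all tables with P ≤ 0.01. With carrier and outcome shares of 10 to 50 % (assumed), the true size at nominal 0.01 is about 0.004 to 0.008 with 120 patients. It is about 0.005 or less with 30, the size of the inflammatory subset.

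- *One phenotype, size 0.006:* 1 − 0.994^10 = 5.8 % with 2 SNPs per gene, and 1 − 0.994^15 = 8.6 % with 3.
- *Three phenotypes, assumed sizes 0.0055 (consumption), 0.006 (PPSP) and 0.003 (inflammation):* 1 − (0.9945 × 0.994 × 0.997)^(5s), with s SNPs per gene, gives about 7 %, 14 % and 20 % for s = 1, 2 and 3.

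The second line applies only if every phenotype were tested by Fisher's test on a 2×2 table, which the article does not say.

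**Step 5: the count may be low.** The inflammatory response is counted above as one phenotype. The article measures six cytokines in two fluids at five times, so several tests may stand behind it.

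**Step 6: threshold with the full count.** 0.05/m is 0.005 for 10 tests, 0.0033 for 15, 0.0017 for 30 and 0.0011 for 45.

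**The case against.** The case against has four parts.

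1. **The size is uncertain.** The SNP count is unknown, and linkage and Fisher's conservatism both pull the error down. This stands. With Fisher's test, one phenotype and 2 SNPs per gene, the error could be close to 5 %. The figures in Step 2 are therefore values under independence and exact test size, not estimates of what will happen. The objection does not rescue the rule, because protection that depends on an unstated SNP count and on a test's conservatism is not what a Bonferroni correction promises.

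2. **Pooling three phenotypes into one family is a choice.** This also stands. Correction within each phenotype is common in secondary candidate-gene work. Even so, a gene divisor falls short once there is more than one SNP per gene. It would suit a single gene-level test, and the combined-polymorphism analysis might be of that kind, but the article does not say so.

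3. **Dichotomised outcomes.** Because Fisher's test and logistic regression are the only methods named for genetics, a reader might infer that morphine consumption and cytokines will be cut into categories, with a loss of information. The article does not support this. It gives no cut-point, and its general rule for quantitative variables is the t test or Mann-Whitney test. Fisher's test and logistic regression fit PPSP. What is missing is only a statement of which method goes with which phenotype.

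4. **Randomised arm.** A reader might also infer that arm is ignored. The article lists no covariates for the logistic model, so nothing can be said to be excluded. Randomisation makes arm independent of genotype in expectation, so leaving it out would mainly cost precision.

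**Conclusion.** The point holds for the divisor. As written, the correction guarantees 5 % only with one SNP per gene and one phenotype. Under independence and exact test size, the error is about 10 % and 14 % within a phenotype for 2 and 3 SNPs per gene. Across the three phenotypes it is about 14 %, 26 % and 36 % for 1, 2 and 3. These figures rest on assumed SNP counts, and the true values are likely to be lower for the reasons in Steps 3 and 4.

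The matching of methods to phenotypes needs clarifying but is not shown to be wrong. The genetic analysis is secondary. The Discussion speaks of investigating whether polymorphisms might be biomarkers, so it would go too far to say that false markers will be put forward.

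**What to change.** - List the SNPs, and one declared summary measure for each phenotype.
- Set the Bonferroni divisor to the number of SNP tests within each declared phenotype family, or to SNPs x phenotypes if one family is claimed. A permutation max-T over the same tests is an alternative that allows for linkage and gives up less power.
- Label genetic results outside the declared family as exploratory.
- State that Fisher's test and logistic regression apply to PPSP, and that morphine consumption and cytokines are analysed on their own scale, transformed if needed, by linear or rank-based methods, preferably with arm as a covariate.

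This changes wording in the analysis plan only and needs no new data. The price is a stricter threshold, for example 0.0033 instead of 0.01 for 15 SNPs within one phenotype, or 0.0011 for 45 tests in one family, and so less power for each SNP.

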## Discussion

Historically, care providers have considered pain a perioperative issue able to influence immediate morbidity, but in the last decade greater attention has been placed on the long-term effects of unrelieved postoperative pain, especially PPSP [4, 5]. Postoperative pain is a composed phenomenon, in which different variables have to be taken into account [28]. Therefore, new multidisciplinary studies should address pain in a different perspective, heading toward a pathophysiological approach to the different components of pain perception and not merely to analgesia expressed as a numeric value in the first days after surgery. Unfortunately, not all of these components are known, and therapeutic approaches still need to be improved.

When clinicians deal with acute postoperative pain, the surgical wound is a pivotal target for analgesia; nociceptors located within the surgical incision are the origin of pain stimuli coming from the periphery, and their prolonged activation is one of the causes of central sensitization. Inflammation also is a main determinant of pain; a lot of mediators are increasingly expressed after tissue injury leading to primary hyperalgesia [12], and IL-1 has been linked to pain persistence [14]; thus, a therapeutic approach specifically aiming to reduce the inflammatory response is rational. CWI with non-steroidal anti-inflammatory drugs seems to provide only partial advantages [11] (because they act only on COX-associated mediators, like prostaglandin E), whereas steroids have a wide anti-inflammatory effect and arguably a great efficacy against pain perception and chronicization [8, 16]. In our study, we decided to test the efficacy of CWI with both local anesthetic and steroids in patients undergoing major abdominal surgery, configuring the first phase III clinical trial on continuous deep wound infusion of methylprednisolone.

Peripheral administration should minimize systemic adverse effects by reducing bioavailability and plasma concentration; otherwise, any data about pharmacokinetics and potential side effects of continuous infusion of steroids are available: we therefore decided to exclude patients with any disease potentially precipitating after steroid systemic absorption, primarily diabetes (type 1 or 2).

In regard to local side effects, the main concerns are about wound healing and infections potentially associated with immune-modulatory action of steroids. Most of the existing data deal with high doses of systemic steroids [29, 30]. Up to now, few studies have addressed these issues in patients receiving peripheral steroids: these studies are in the orthopedic setting and investigate only clinical effects of a single-shot administration and provide no evidence of increased infections or difficult healing [29, 30]. We therefore plan to clarify the risk/benefit ratio of continuous administration of methylprednisolone, strictly monitoring wound healing and any potentially harmful effect of CWI.

We decided to treat all the patients with 24-h CWI of ropivacaine and methylprednisolone. This will enlarge the sample size for the phase III trial (120 patients) and will allow us to investigate the differences in locally released cytokines according to suspension of local anti-inflammatory treatment after the first 24 h. This, in our opinion, does not configure a methodological bias, as our primary endpoint is analgesic consumption at 7 days, and we will take care to evaluate any statistically significant difference in morphine consumption at 24 h to eliminate any confounding factor this kind of study design may potentially imply.

Furthermore, an ethical issue arises: because CWI with local anesthetics is already documented as a valuable analgesic strategy [8], switching to a saline infusion after 24 h in the control group may be questioned. Otherwise, placebo control is still a key feature for high-quality clinical trials in the perspective of determining the actual effectiveness of treatments. Furthermore, because we are investigating local inflammation, comparing analgesic efficacy with cytokine analysis will help clarify whether the pain-killing effect of CWI is associated either with methylprednisolone’s action or with a “washout” phenomenon (i.e., on the steroid’s effect on cytokine release rather than on cytokine dilution by fluid infusion).

We decided to analyze both local and systemic inflammatory response for the following reasons. First, systemic inflammation is advocated to be a risk factor for postoperative and persistent pain [5], but few data exist, and failed in the identification of standard values of inflammatory markers as predictors of pain; therefore, we guess our data could configure as a reference for future studies. Second, we want to investigate whether local and systemic cytokine expressions are linked or not, and how. Third, we aim to investigate the effect of a peripheral block on systemic inflammation because previous studies have provided an incomplete understanding [11]. Furthermore, there is evidence of the role of free radicals as a crucial mediator of pain of different etiologies [31–33], and we will also investigate the free-radical formation and correlate these data to the inflammatory response.

The maintenance of CWI up to 7 days could also be questioned because we traditionally consider the first 48 h after surgery to be the most challenging and to be associated with the highest pain values, and most of the studies consider a 2-day infusion after surgery; otherwise, studies on incisional pain have demonstrated that sensitization processes tend to restart after suspension of analgesia [34]. Therefore, an effective nociceptive block should cover the entire perioperative period, aiming to fight pain until it lasts. Use of patient-controlled wound infusion arguably allows prolongation of the analgesic infusion as deemed necessary by the patient, without drug overdosing, and will help quantify the average amount of drugs needed in the first 7 days after major abdominal surgery. This final issue is to be considered carefully because our study is part of a wider one aimed to validate a new nanotech device for pain treatment: this device is being created by bio-engineers and will be tested for bio-compatibility in rats. The final aim is to develop a new analgesic tool to be based on nanotechnology and to be applied on the surgical wound in humans for sustained release of pain medications and growth factors after surgery and to be finally re-absorbed by tissues. In this perspective, our study is the first step of a longer project and is focused on investigating (1) the efficacy and safety of topical methylprednisolone, (2) the average dose of pain medications required in the perioperative period, and (3) the average needed duration of a wound infusion.

With this study, we aim to validate the use of methylprednisolone for CWI to reduce morphine consumption and associated side effects as well as PPSP after abdominal surgery. Moreover, we want to investigate whether genetic polymorphisms might be biomarkers for postoperative pain and opioid consumption. These results should be used to define delivery times and dosages for the new nanotechnology platform we are currently developing for sustained postoperative pain relief to be used in clinical practice and should be able to improve perioperative and long-term outcome for patients.

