### Procedures - clinical study

On the day of surgery, patients come to the operating room and are provided with standard monitoring (electrocardiogram, oxygen saturation, non-invasive blood pressure, and invasive pressure monitoring). General anesthesia is given using propofol and midazolam (as deemed appropriate by the anesthesiologist), opioids (fentanyl 0.2 μg/kg or remifentanil 0.1-0.25 mg/kg per min or both), and muscle relaxants (cisatracurium/rocuronium) and maintained with sevoflurane.

A morphine bolus of 0.15 mg/kg is given 30 to 45 min before the end of surgery. An infusion catheter (Baxter Painfusor®; Baxter International, Deerfield, IL, USA) is placed by the surgeon in the fascial plane between peritoneum and fascia trasversalis, and a 10-ml bolus of 0.2 % ropivacaine is administered immediately after muscular plane closure; the catheter is then connected to an electronic pump (CADD®-Solis; Smiths Medical, Dublin, OH, USA) to give a continuous infusion of pain medications.

During the first 24 h, all patients receive ropivacaine 0.2 % + methylprednisolone 1 mg/kg, 10 ml/h (total volume of 240 ml in 24 h) continuous wound infusion; additionally, either acetaminophen 1000 mg or ketorolac 30 mg every 8 h is prescribed.

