### After 24 h, patients are randomly assigned between two groups of treatment:

Treatment group: 10 ml/h continuous infusion of ropivacaine 0.2 % + methylprednisolone 1 mg/kgPlacebo group: 10 ml/h continuous infusion of saline 0.9 %.

Regardless of treatment group, rescue analgesia in the first 48 h is provided by PCA pump with morphine (0.5 mg/ml, bolus 1 mg, lock-out 5 min, 20 mg limit every 4 h).

Random group allocation of patients is made through a computer-generated sequence. To maintain blinding, a research fellow who is not taking part in patient evaluation is in charge of preparing and programming all of the pumps used during the study: an opaque, sealed, sequentially numbered envelope is assigned to each patient and is opened by the same research fellow after the first 24 h of treatment.

Patients and their anesthesiologists are blind to treatment assignment. A clinical resident, who is not involved with randomization, is in charge of all clinical evaluations as part of the daily clinical practice.

The envelope is maintained apart from the patient’s case report form and is to be opened in every potentially harmful situation for the patient but only when care providers need to be aware of the patient’s treatment. All ropivacaine and methylprednisolone vials used during the study are registered with their code in order to be tracked and recognized in the future for any issue potentially hindering the validity of data.

At 48 h, morphine PCA is removed, and all patients are treated with Patient-Controlled Intrawound Analgesia (PCA through the wound catheter) with either ropivacaine 0.2 % alone or saline according to the group of randomization up to a maximum of 7 days after surgery. The catheter is removed at the seventh postoperative day or after 36 h of non-use (no self-administered bolus). After PCA removal, rescue additional analgesia is provided by tramadol (100 mg or 50 mg according to patient’s weight of not more than or of more than 50 kg).

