### Study outcomes

The primary outcome of the study is to investigate whether a wound infusion of local anesthetic and steroid has a higher analgesic efficacy compared with placebo during 7 days following surgery, assessed as analgesic consumption: the primary endpoint will be the reduction of morphine equivalents required in the first 7 days after surgery.

Secondary outcomes will include the differences in analgesia and side effects within 7 days after surgery. We will investigate any difference in pain at rest and movement (i.e., coughing and deep inspiration) by Numeric Rating Scale (11-point scale from 0 = no pain to 10 = worst imaginable pain), additional analgesic consumption, side effects (postoperative nausea and vomiting, sedation, and any signs of local anesthetic or steroid systemic toxicity), and incidence of persistent post-surgical pain. Differences in terms of wound healing or wound infections will be also assessed up to 3 months to assess any local side effect of steroid infusion. The degree of inflammatory response/oxidative stress between groups will be assessed to analyze the effect of CWI with either treatment or placebo. We plan to analyze the combined effect of some polymorphisms (by using a gene-candidate approach) of genes related to the development of PPSP, pain sensitivity, opioid response, and inflammatory reaction.

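### The 7-day primary endpoint includes 24 h of identical pre-randomisation treatment; the planned significance check at 24 h is no safeguard, and 0-24 h consumption should be a fixed covariate

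*Protocol article*

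**What the plan says.** All statements are in the protocol article.

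- Procedures - clinical study: "During the first 24 h, all patients receive ropivacaine 0.2 % + methylprednisolone 1 mg/kg, 10 ml/h".
- The section that follows: "After 24 h, patients are randomly assigned between two groups of treatment". The allocation envelope "is opened by the same research fellow after the first 24 h of treatment". Morphine PCA is the rescue analgesic throughout the first 48 h, so morphine use is already accruing before allocation.
- Study outcomes: "the primary endpoint will be the reduction of morphine equivalents required in the first 7 days after surgery".
- Statistics, sample size: the "average morphine equivalent consumption in patients receiving local anesthetic and steroids CWI will be reduced by" 50 %. The stated sources showed reductions of 30-50 % with local anaesthetic wound infusion. The result is 50 per group for 80 % power at 5 % α. No mean, SD or time window is given.
- Statistics, analysis: "We will perform group comparison by using the" Student's t test or the Mann-Whitney test for quantitative variables. No adjustment of the primary comparison is described.
- Discussion: the authors hold that the common first day introduces no methodological bias, because the endpoint is consumption at 7 days and because "we will take care to evaluate any statistically significant difference in morphine consumption" at 24 h, with the aim of removing confounding.

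**The concern.** Consumption from 0 to 24 h is a baseline measurement. It accrues under identical treatment and with allocation undisclosed, so the randomised treatment cannot change it. Three things follow when it is summed into the outcome.

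1. A significance test at 24 h is the wrong safeguard. Any difference there is due to chance by construction. A non-significant imbalance still shifts an unadjusted comparison, and the article does not say what follows from a significant one.
2. If early and later use are positively correlated, a value that could explain part of the outcome's variance is instead added to it.
3. A given percentage cut after 24 h is a smaller percentage of the 7-day total. The planning effect is already the top of the cited range, and the sample-size text does not say to which window it applies.

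At stake are the precision of the primary result, the meaning of the 50 % planning effect, and a stated reassurance that does not do what it claims.

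**Working it through.** **Inputs from the article:** 50 per group, 80 % power, α 5 % (taken as two-sided; the article does not say), 50 % reduction, cited range 30-50 %, attrition 15-20 %.

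**Assumptions, not in the article:** f, the share of control-arm 7-day use falling in 0-24 h, from 0.1 to 0.5; r, the correlation of 0-24 h use with the outcome analysed, from 0.3 to 0.7; and an SD equal in both arms.

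**Step 1. The plan's own figure.** Without a mean and SD, 50 per group cannot be reproduced, only back-solved. A two-sample t test with 50 per group and 80 % power detects a standardised difference of 0.566. If this is 50 % of the control mean, SD = 0.5/0.566 = 0.884 of the control mean. Inflating for attrition gives 50/0.85 = 59 and 50/0.80 = 63 per group. That fits about 120 in total, not 120 per group.

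**Step 2. The 50 % refers to the 7-day total.** Power is then 80 % by construction. Since nothing can change before 24 h, the cut needed afterwards is 0.5/(1-f):

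| f | Cut needed after 24 h |
|---|---|
| 0.1 | 56 % |
| 0.2 | 63 % |
| 0.3 | 71 % |
| 0.4 | 83 % |
| 0.5 | 100 % |

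Every value lies above the cited 30-50 %.

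**Step 3. The 50 % acts only after 24 h.** The reduction in the total is 0.5 × (1-f), and the standardised difference is 0.5(1-f)/0.884. For f = 0.2 this is 0.40/0.884 = 0.45. Power of the unadjusted t test on the 7-day total:

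| f | Reduction in total | 50 per group | 60 per group | 100 per group |
|---|---|---|---|---|
| 0.1 | 45 % | 71 % | 79 % | 95 % |
| 0.2 | 40 % | 61 % | 69 % | 89 % |
| 0.3 | 35 % | 50 % | 58 % | 80 % |
| 0.4 | 30 % | 39 % | 45 % | 67 % |
| 0.5 | 25 % | 29 % | 34 % | 51 % |

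The column for 60 is 120 in total with no loss. The column for 100 is 120 per group less about 17 %.

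**Step 4. What adjustment gains.** The standard error is multiplied by √(1-r²), which is worth a factor 1/(1-r²) in sample size:

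| r | SE factor | Cut in SE | Equivalent sample size |
|---|---|---|---|
| 0.3 | 0.954 | 5 % | × 1.10 |
| 0.5 | 0.866 | 13 % | × 1.33 |
| 0.7 | 0.714 | 29 % | × 1.96 |

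**Step 5. The endpoint label need not change.** Write the 7-day total as T = B + P, with B the 0-24 h use and P the use from 24 h to day 7. If P = a + b·arm + c·B + error, then T = a + b·arm + (1 + c)·B + the same error. The arm coefficient b and its standard error are identical.

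**Step 6. What the 24-h check lets through.** Take r = 0.6 and a 24-h imbalance of z = 1.5 (P = 0.13, which passes as non-significant). The unadjusted statistic is shifted by 0.6 × 1.5 = 0.9, and its conditional type I error is P(|0.9 + 0.8Z| > 1.96) = 9.3 %. At z = 0 it is P(|0.8Z| > 1.96) = 1.4 %. Averaged over all imbalances it is 5 %.

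**The case against.** **Validity.** The authors can say that no bias arises, and strictly they are right. Randomisation makes the unadjusted 7-day difference unbiased with 5 % unconditional type I error. The absolute difference is not diluted; only the relative reduction and the precision suffer. The 9.3 % in Step 6 belongs to one chosen imbalance and is offset by values below 5 % elsewhere. It shows that the check does not protect the comparison, not that the trial's error rate is inflated. This part of the objection stands.

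**Power.** A reader might infer that the trial does not deliver its stated 80 %. The article does not support that. It gives no mean, SD, window, first-day share or correlation, and if the 50 % refers to the 7-day total, 80 % holds by construction. The per-group number is also unsettled: Statistics asks for 120 in each arm, while the Abstract and Discussion speak of 120 patients. In addition, 50 per group may be pessimistic for a 7-day endpoint, because dropout is defined by the 3-month evaluation and all enrolled patients are to be analysed. The power figures are therefore conditional.

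**Gain.** The correlation is unknown. At r = 0.3, adjustment is worth only about 10 % more patients.

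**Condensed text.** The sentence on tests covers quantitative variables in general, and an analysis plan that is not shown could add covariates. That is fair, so the absence of a covariate list is not the point. The Discussion does, however, set out the 24-h significance check as its answer to this design feature, and that answer can be judged as written.

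**Conclusion.** The point holds as a fault in precision and in the stated safeguard, not in validity. The primary endpoint contains a pre-randomisation day that cannot respond to allocation, and the check offered for it corrects nothing.

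The size depends on two quantities that the article does not give. For f, the planning effect either demands a post-24 h cut above the cited range (56 % at f = 0.1, 100 % at f = 0.5), or leaves unadjusted power with 50 per group at about 71 % down to 29 % over the same range (79 % to 34 % with 60 per group). For r between 0.3 and 0.7, failing to adjust forgoes a reduction in standard error of about 5-29 %. No single power figure should be quoted until the window of the 50 % and the number per group are settled.

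**What to change.** 1. Make the primary analysis an ANCOVA of morphine equivalents on arm with 0-24 h consumption as a covariate, always and without a pre-test. The outcome may be the 7-day total or the use from 24 h to day 7.
2. Remove the 24-h significance check as a safeguard. Consumption at 24 h can still be reported descriptively by arm.
3. State whether the 50 % refers to the 7-day total or to the period after randomisation, and give the control mean and SD for that window.
4. Resolve 120 per group against 120 in total, then restate power as a range over plausible f and r.

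The cost is wording. Analgesic consumption is already recorded at the scheduled evaluations, including 24 h, and the article reports the double-blind trial as still recruiting, with 46 patients enrolled. The drawback is that the restated power may look less favourable, and a percentage effect will have to name its window.
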